## Abstract

**Background:**

Exercise confers myriad health benefits and physical inactivity is a modifiable risk factor for many non-communicable chronic diseases. However, individual responsiveness to guideline-based exercise programs is idiosyncratic for health and fitness outcomes. It is not known whether the response of individuals to distinct exercise modalities tend to be concordant or whether there is a genetic contribution to variation in exercise responsiveness.

**Methods/design:**

Healthy, young adult (16–40yrs) monozygotic (MZ) and dizygotic (DZ) twin pairs were recruited and randomly assigned to 3 months of endurance or resistance exercise training. Twin pairs trained together. After 3 months of training in their randomly assigned mode, a washout period of 3 months was observed before twin pairs crossed over to complete 3 months of the alternate exercise intervention. Measures of cardiac morphology and function, cerebrovascular function, cognitive performance, peripheral artery function, biochemistry, blood pressure, body composition, skeletal muscle strength and cardiopulmonary fitness were collected before and after each exercise intervention (i.e. at weeks 0, 12, 24 and 36).

**Discussion:**

We adopted exercise modalities that produce distinct haemodynamic and physiological stimuli for physiological adaptation and recruited MZ and DZ twin pairs to address questions such as; *do individuals exhibit concordant responses to distinct exercise modalities?* and *what is the genetic contribution to adaptation resulting from distinct training modalities?* The results of this study will provide insight into the genetic and environmental contribution to exercise response to distinct modes of training, with implications for determining the optimal approaches to exercise prescription.

## Abbreviations

MZmonozygoticDZdizygoticENDendurance trainingRESresistance trainingUWAUniversity of Western AustraliaMRImagnetic resonance imagingVO_2_oxygen uptakeHRheart rateRPErating of perceived exertion1RMone repetition maximumBPblood pressureTEEtotal energy expenditureAEEactive energy expenditureSBPsystolic blood pressureDBPdiastolic blood pressureCCAcommon carotid arteryFMDflow-mediated dilationGTNglyceryl trinitratePWApulse wave analysisPWVpulse wave velocityLVleft ventricleRVright ventricleEDVend-diastolic volumeESVend-systolic volumeLVIDleft ventricular internal dimensionPLAXparasternal long-axisPSAXparasternal short axisASEAmerican Society of EchocardiographyA4Capical four-chamberLAleft atriaA2Capical two-chamber

## Introduction

1

Physical inactivity is a crisis that is responsible for 6–10% (>5 million deaths) of annual global mortality from non-communicable diseases such as coronary heart disease and stroke. It caused 9% of premature mortality, or more than 5.3 million of 57 million deaths, worldwide in 2008 [1]. Unlike most commonly prescribed medications which target specific health outcomes, exercise can positively influence a wide range of important health determinants (weight control, cardiovascular health, cerebrovascular health, cognition) that contribute to preventing development of chronic diseases [2]. In spite of the well-established role of exercise and physical activity in prevention of chronic disease, recent studies suggest that up to 30% of individuals may fail to exhibit beneficial physiological responses to exercise interventions that emulate guideline recommendations for health [3]. These individuals can be considered “low-responders” for particular health parameters, in response to the type of exercise performed. This phenomenon was recently confirmed for the impacts of training on arterial health [4] and the idiosyncratic response of cardiorespiratory fitness (VO_2_) to endurance training has also been recently summarised [5].

In the context of responsiveness to exercise, a study from our laboratory suggested that health-related benefits may be modality specific. Spence et al. (2011) utilised two dichotomous exercise intervention modalities, endurance (END) and resistance (RES) training, which induce distinct haemodynamic and physiological stimuli for physiological adaptation. We found that cardiac adaptation differed between modalities [[6], [7], [8], [9]]. However, subjects in this study were randomised to parallel groups and completed only one exercise intervention/modality. It is therefore possible that the distinct responses to alternate exercise modalities that we observed might have been biased by the randomisation process. A within-subject cross-over design is a more appropriate approach to address the question of whether the response to distinct exercise modalities differs within individuals. Using this design, we can also determine whether individuals demonstrate concordant or discordant responses to distinct forms of training (i.e. whether low-response to one form of exercise training necessarily implies low-response to all modalities). This has implications for the optimisation of exercise prescription in humans, whereby switching to an alternate form of exercise could “rescue” subjects who otherwise may not have benefited.

In addition to the responder/non-responder phenomenon, and the question of whether low-response to one form of exercise training necessarily implies low-response to all modalities, a question relates to genetic predisposition to adaptation. Classical twin studies utilising monozygotic (MZ) and dizygotic (DZ) twin pairs have long been used to assess the contribution of unmeasured genetic and environmental effects on variation in measured traits [10,11]. Since MZ twins theoretically share 100%, and DZ twins ~50%, of their DNA [12] then a phenotype that is purely explained by genetics would hold a ratio of 2:1 consisting of correlations of 1 for MZ and 0.5 for DZ [13]. If the 2:1 ratio remains the same but the correlations are lower than these values, then both shared and unshared components may be influencing results [14,15]. In this way, classical twin studies allow researchers to stratify the total variance of a phenotype. Any excess correlation observed for MZ compared with DZ pairs is assumed to be due to the extra genetic material shared by MZ twins (under the equal environments assumption [16]), and the amount and proportion of variation in a measured trait due to additive genetic effects (A), shared environmental effects (C) and unshared effects (E) can be determined. The proportion of the total variation which is due to A is often referred to as the heritability [12,17]. Alternately, in cases where genetic and environmental effects cannot be separated, the use of a classical twin study design may make it possible to estimate the extent of familial aggregation [18].

The heritability of a phenotype has typically been assessed cross-sectionally, without any intervention [[19], [20], [21], [22], [23], [24], [25], [26], [27]]. The majority of studies purporting to assess the impact of heritability on the response to exercise have not, in fact, exercise trained individuals. Others have only utilised a single training modality, or focussed on discrete outcomes such as VO_2_ in twin or family studies [[28], [29], [30]]. Only a handful of exercise studies have assessed the heritability of additional outcome measures, including a study by our team that investigated peripheral vascular function and health in MZ and DZ twin pairs in response to an END training program [24,31]. Some additional outcomes in twin and family studies are examined in a systematic review and meta-analysis [32]. However, there are no studies, to our knowledge, that have utilised MZ and DZ twin pairs to assess the heritability of response to two distinct exercise modalities. The novel aspect of the present study design is that twin pairs trained together, using matched training intensity, so that each individual within a twin pair received an identical stimulus across the same time period. We also collected data on multiple health and fitness outcomes.

This paper describes the rationale and methodological aspects of a randomised controlled cross-over trial aimed at investigating the idiosyncratic nature and heritability of responses to distinct exercise training modalities (‘END’ and ‘RES’ exercise) in twin pairs. If exercise is considered medicine, then this study assesses the human response to different prescriptions, so that in the future, specific modes of exercise can be tailored on the basis of individualised health and/or fitness benefits.

## Methods/design

2

### Objectives

2.1

1.Primary objective: Assess the contribution of genetic and environmental effects on variation in cross-sectional data, and END and RES training responses, for each outcome measure2.Secondary objectives:a.Assess whether individual response to training differs between modalities for each outcome measureb.Assess whether the concordance between response to END and RES modes of training will differ between individuals

### Hypotheses

2.2

1.The heritability of response to training will differ according to whether cross-sectional or training data are assessed.2.Response to exercise will be modality specific for each outcome measure.3.Concordance between response to END and RES modes of training will differ between individuals.4.Concordance between twins in a pair in terms of the response to END or RES modes of training will differ between MZ and DZ pairs.

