##### Endothelium-dependent vasodilation: flow-mediated dilation

2.7.10.2

To assess endothelium-dependent vasodilation of the brachial and femoral arteries, the flow-mediated dilation (FMD) technique was used (Supplementary Fig. 3), described in more detail elsewhere [56]. The reliability of FMD tested ~7 days apart in healthy subjects has a high correlation (r = 0.82) [58]. In summary, a rapid inflation-deflation pneumatic cuff (D.E. Hokanson Inc., Bellevue, WA, USA) was wrapped around the left forearm, 2 cm distal to the olecranon process. A second larger cuff was positioned on the upper left thigh ~15 cm distal of the inguinal ligament, or ~5 cm proximal to the patella and patella tendon. The arterial-lumen interface was optimised for longitudinal B-mode images of the brachial and femoral arteries. Continuous Doppler pulse wave velocity of each artery was simultaneously obtained (by two expert vascular sonographers) using the lowest possible isonation angle (60°). Dynamic range and Doppler gain settings were consistent between machines, and specifications were replicated for each individual on repeat visits. The left arm was placed at the height of the heart in approximately 80⸰ abduction from the body. The arm was supported underneath the muscles and the hand slightly pronated in a relaxed position for the participant. The brachial artery was scanned in the middle or upper third of the arm, depending on positioning of the brachial artery bifurcation. The brachial artery was also scanned either through the biceps brachii or between the biceps and triceps brachii muscles, depending on which gave a cleaner image for analysis for that particular participant. The femoral artery was assessed in the proximal third of the thigh, at least 5 cm distal from the bifurcation, with the left leg in slight (<5°) lateral rotation. These anatomical specifications were noted at the initial testing session and replicated at the repeated visits.

A baseline scan was recorded for a period of 1 min to assess resting blood vessel diameter, shear rate and blood flow velocity. Both blood flow occluding cuffs were rapidly inflated to a suprasystolic pressure of 220 mmHg for 5 min. Recording resumed 30s prior to cuff deflation so that it wasn't missed and continued for 3 min post-deflation [59]. Peak artery FMD (absolute and %), shear stress, time to peak and artery diameter pre-post cuff were analysed as previously described [56,58,59].

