
## Planned statistical analysis

3

Statistical analyses are to be performed with SPSS 20.0 (IBM Australia Ltd, New South Wales, Australia) and STATA 11 software (StataCorp, College Station, Texas). All data will be reported as group means with confidence intervals, with default statistical significance assumed at *P* < 0.05. Cross-sectional results for each outcome measure refer to baseline entry (week 0) data. Response to training data is post minus pre for END and RES training. Normality of groups (MZ and DZ) will be assessed via Shapiro-Wilk test of normality where normality of spread is assumed at *P* > 0.05. Between-group (MZ vs DZ) differences will be assessed with the conservative non-parametric Mann-Whitney *U* test and regression models including the single covariate zygosity (MZ/DZ), fitted using a generalised estimating equation (GEE) approach to account for correlation of twins within-pairs. The effect of the exercise interventions on each outcome measure will be assessed using a linear mixed models approach.

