The primary objective of the current study is to estimate the MZ and DZ correlations and the variance components A, C and E for each outcome measure cross-sectionally, and in response to exercise training (END and RES). In STATA mixed models effects will calculate intraclass correlation coefficients (r) for MZ and DZ twin pairs. Covariates to be adjusted for (e.g. sex, fat-free mass, VO_2max_, baseline data) will depend on the primary outcome measure. The subsequent rMZ and rDZ, and their respective P-values and 95% confidence intervals will be presented. Differences between intraclass correlations (rMZ vs rDZ) will be assessed using the likelihood-ratio test in STATA to compare mixed effects models constraining covariances for MZ and DZ pairs to be equal with models allowing different covariances for MZ and DZ pairs [69]. If the model allowing different MZ and DZ covariances are significantly better, and rMZ are significantly different to rDZ, A, C and E will then be calculated from the estimates of the DZ covariance and the additional MZ covariance, and confidence intervals for A, C and E will be estimated using the delta method. When rMZ and rDZ are not significantly different then a single model that includes all twin pairs but constrains the covariance to be equal for MZ and DZ pairs will be used in STATA to calculate C and E components only, and their respective 95% confidence intervals. An additional model which estimates covariance for MZ twins but fixes the DZ covariance to be zero will test if the estimated correlations suggest that the equal environments assumption has been violated.

Secondary objectives of this study will be addressed using the individual change with training (END and RES) results for each outcome measure. Response rates for each modality can be derived as a percentage of positive responses (>0) and compared against one another by a Z-test. Concordances can be derived as the percentage of individuals who positively respond to both exercise training modalities (Supplementary Fig. 5). In a similar way to the correlation analyses, within-twin pair concordances for MZ and DZ can be derived for each exercise intervention and compared to each other.

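### Hypothesis 1 compares cross-sectional with training-response heritability, but the planned analysis states no contrast between them and calculates A only where a low-powered test is significant

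*Protocol article*

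**What the plan says.** The Hypotheses section (2.2) opens with a comparative claim: "The heritability of response to training will differ according to whether cross-sectional or training data are assessed". I read this as a comparison of heritability at baseline with heritability of the training response.

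Planned statistical analysis (section 3) defines the two kinds of data. The baseline definition is this: "Cross-sectional results for each outcome measure refer to baseline entry (week 0) data". The definition used for the training analyses is a raw change score: "Response to training data is post minus pre for END and RES training". The task set by the primary objective has this wording: "estimate the MZ and DZ correlations and the variance components A, C and E for each outcome measure cross-sectionally, and in response to exercise training". rMZ and rDZ are presented with P-values and 95% confidence intervals for each data set.

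The one comparison stated for these correlations is within a data set: "Differences between intraclass correlations (rMZ vs rDZ) will be assessed using the likelihood-ratio test in STATA". If it is significant, "A, C and E will then be calculated from the estimates of the DZ covariance and the additional MZ covariance". If it is not, the rule begins "When rMZ and rDZ are not significantly different then a single model that includes all twin pairs" and goes on to constrain the MZ and DZ covariances to be equal and to give C and E only.

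Sections 3.1 (washout, carryover and order) and 3.2 (sample size) add no comparison between baseline and response heritability.

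**The concern.** A hypothesis that two heritabilities differ needs an estimate of their difference. The plan produces separate analyses, each with its own significance condition. Where one data set meets the condition and the other does not, one side has an A and the other has a model with no genetic component. The natural reading is then that heritability differs, although significance in one data set and not in the other is no test of the difference.

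There is a second, separate issue. Measurement error falls into E. A week-0 value carries the error of one measurement and a post-minus-pre score the error of two, so the two heritabilities are not on the same footing. At stake is the first stated hypothesis of the trial, on whether a genetic contribution seen at baseline carries over to training response.

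**Working it through.** **1. The plan's own figure.** The article gives no power or precision figure for hypothesis 1. Section 3.2 covers rMZ = 0.80 against rDZ = 0.30 only. With Fisher's z, n = 2[(z_alpha + z_power)/(atanh 0.80 - atanh 0.30)]^2 + 3, where n counts pairs and atanh 0.80 - atanh 0.30 = 1.099 - 0.310 = 0.789. One-sided alpha 0.05 and 80% power give 22.9, so 23, the stated number; two-sided gives 28.2, so 29. At the 31 MZ and 14 DZ pairs in Table 1, two-sided power for this large contrast is about 60% (65% with the intraclass-correlation variance). The test that decides whether A is calculated is thus weak even under the plan's own assumption.

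**2. How often exactly one data set meets the condition.** Assumptions: 31 and 14 pairs, C = 0, the same true-score heritability in both data sets, week-0 reliability 0.82 (the FMD figure), and the two data sets simulated as independent. With a Fisher-z approximation to the test (6,000 runs per setting), p is the proportion significant at week 0 and q for change. The expected proportion with exactly one significant is p(1 - q) + q(1 - p).

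| True heritability | Change reliability | p | q | p(1-q) + q(1-p) | Simulated |
|---|---|---|---|---|---|
| 0.6 | 0.82 | 0.136 | 0.138 | 0.236 | 0.238 |
| 0.6 | 0.64 | 0.143 | 0.098 | 0.213 | 0.211 |
| 0.6 | 0.40 | 0.134 | 0.065 | 0.182 | 0.183 |
| 0.8 | 0.82 | 0.257 | 0.267 | 0.387 | 0.382 |
| 0.8 | 0.64 | 0.271 | 0.150 | 0.340 | 0.344 |
| 0.8 | 0.40 | 0.261 | 0.078 | 0.298 | 0.302 |

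With the 1-df likelihood-ratio test that the plan names, repeated simulations gave roughly 20-27% at heritability 0.6 and 35-46% at 0.8. The pattern is the same: one set of 1,000 runs per setting gave 28%, 25% and 22% at heritability 0.6, and 42%, 37% and 34% at 0.8, as change reliability fell from 0.82 to 0.64 to 0.40. Disagreement is most frequent when reliability is equal, so it arises from the significance condition and low power, not from change-score error.

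**3. Reliability of a change score.** Let R be the test-retest reliability and rho the observed pre-post correlation, with equal pre and post variances of 1. The change has variance 2(1 - rho), of which 2(1 - R) is error, so its reliability is 1 - (1 - R)/(1 - rho) = (R - rho)/(1 - rho). Observed heritability is true heritability times reliability. The article gives R but not rho, so a range is shown.

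- FMD, R = 0.82 (section 2.7.10.2), true heritability 0.60. Week 0: 0.60 x 0.82 = 0.49.
  - rho = 0.3: reliability 0.52/0.70 = 0.74, observed 0.45
  - rho = 0.5: 0.32/0.50 = 0.64, observed 0.38
  - rho = 0.7: 0.12/0.30 = 0.40, observed 0.24
  - rho = 0.8: 0.02/0.20 = 0.10, observed 0.06
- LV mass and EDV, R = 0.99 (section 2.7.11.1): reliability of change 0.98, 0.90 and 0.80 at rho = 0.5, 0.9 and 0.95.

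Likelihood simulation agrees: at heritability 0.8 and change reliability 0.40, mean A was 0.67 at week 0 and 0.33 for change (expected 0.8 x 0.82 = 0.66 and 0.8 x 0.40 = 0.32). More generally, with true variances T at baseline and D for change and error variance e, reliability is T/(T + e) against D/(D + 2e), so there is no extra attenuation once D is at least 2T.

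**4. Bias against sampling error.** In the Fisher-z simulations each estimate 2(rMZ - rDZ) had a standard deviation of about 0.5 to 0.6. An unadjusted Wald test of the difference rejected in about 6-8% of runs, against a nominal 5%, across all settings tried. A direct comparison would therefore seldom be misled by attenuation alone.

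**The case against.** The strongest reply has four parts.

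- **rMZ and rDZ are presented with intervals whatever the test shows**, so a reader can set week 0, END and RES side by side. This stands. No text says that hypothesis 1 will be decided by which data set yields an A. A reader might infer such a rule, but the article does not state it. What remains is that no difference is estimated and that A, the quantity hypothesis 1 names, is withheld on one side by a stated rule.
- **This is a journal article, and a fuller protocol or SAP may hold the contrast.** This also stands, so the point is only that the article's planned analysis states none. The condition on A, however, is fixed in the article itself.
- **Change-score error need not produce a difference.** A reader might infer that response heritability will look lower, and that a finding of lower response heritability would be an artefact. The documents do not support that. The pre-post correlations are not given, the effect is small for LV mass and EDV in most of the range, and hypothesis 1 has no direction. The previous FMD correlations quoted in section 3.2 run the other way: 2(0.60 - 0.38) = 0.44 cross-sectionally and 2(0.74 - 0.37) = 0.74 for response. That difference of 0.30 has an approximate standard error of 1.1 (taking 11 and 6 pairs per group), so it is uninformative in either direction.
- **A correction for reliability cannot carry the decision.** Agreed. The quoted retest correlations are for single measurements from external samples. The divisor (R - rho)/(1 - rho) approaches zero as rho nears R. For the cerebrovascular measures the article gives only coefficients of variation.

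Baseline data as a possible covariate does not answer the point, since it is not a correction for measurement error.

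**Conclusion.** The point holds in this form. The article states a comparative hypothesis, gives no contrast for it, and calculates A only after a significant within-data-set test that has low power at 31 and 14 pairs. With equal true-score heritability, exactly one of two data sets would yield an A in roughly 20-27% of trials at heritability 0.6 and 35-46% at 0.8. These figures assume C = 0, week-0 reliability 0.82, all enrolled pairs analysed and independent data sets. With three data sets (week 0, END, RES), a mixed result is at least as likely.

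Attenuation of response heritability by change-score error is a real but conditional second issue: possibly strong for FMD at moderate to high pre-post correlation, slight for LV mass and EDV in most of the range, and absent where true change variance is at least twice true baseline variance. It is not the main source of the apparent differences. The plan should be changed, but nothing here shows that hypothesis 1 would be wrongly confirmed.

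**What to change.** For each primary outcome:

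1. Estimate A, C and E for week 0, END change and RES change whether or not the likelihood-ratio test is significant. Use the same pairs and a consistent covariate set in all three; the 80% adherence rule in section 2.6 could otherwise leave different pairs in the baseline and training analyses.
2. Assess hypothesis 1 by the difference in standardised A, A/(A + C + E), and in rMZ - rDZ, each with a 95% interval from resampling whole pairs or from a joint twin model of baseline and change. State that significance in one data set and not in another will not be read as a difference.
3. As a sensitivity analysis only, and where a retest correlation is available (FMD 0.82, GTN 0.84, ESV 0.93, EF 0.94, LV mass and EDV 0.99), report a reliability-corrected difference. Divide the week-0 estimate by R and the change estimate by (R - rho)/(1 - rho), with rho taken from the trial's own pre-post data. Do not make it the decision rule.

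The cost is revised analysis wording and some programming, with no new data. The downside is that the intervals will be wide and hypothesis 1 may end as inconclusive.
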